# **Criteria for Discontinuation of Individual Subjects**

The principal investigator or sub-investigator will discontinue subjects from the study if continuation becomes difficult for the following reasons, and take appropriate measures based on the subject’s benefit. Investigations/examinations scheduled will be conducted as promptly as possible (except when consent withdrawal prevents execution). If consent is withdrawn after the start of study drug administration, efforts will be made to clarify whether it was due to lack of efficacy, adverse events, or incidental events (e.g., relocation) and record it as reference for inclusion in efficacy/safety evaluation.
 The investigator will record the discontinuation date, reason, and comments in the case report form.

1) Protocol treatment cannot continue due to adverse events

2) Subject requests discontinuation for reasons unrelated to adverse events (e.g., before starting treatment after registration)

3) Death during protocol treatment

4) Other protocol violations

The discontinuation date is defined as the date of death for 3) or the date treatment discontinuation is determined for other cases.

Rationale:

1, 3) To confirm safety

2, 4) Ethical considerations

# **Handling of Adverse Events**

## **Response to Subjects for Adverse Events**

“Adverse event” refers to any undesirable or unintended sign, symptom, or disease occurring after study drug administration, regardless of causality.
 Investigators will take appropriate measures immediately upon recognizing an adverse event and record it accurately in both medical records and CRF. If study drug administration is discontinued or treatment is required for the adverse event, subjects will be informed.
 In emergencies requiring identification of the study drug, the principal investigator will contact the allocation/coding manager through the study representative to obtain disclosure of the allocation for that subject.

## **Reporting of Serious Adverse Events**

　“Serious adverse events” include any undesirable medical event regardless of dose that meets any of the following:

(1) Death

(2) Life-threatening

(3) Requires or prolongs hospitalization

(4) Results in persistent or significant disability/incapacity

(5) Causes congenital anomaly in offspring

Investigators will promptly report all serious adverse events during surgery or postoperative hospitalization to the hospital director (or Clinical Trial Review Board at Osaka City University) regardless of causality with the study. In multicenter trials, if causality cannot be ruled out, the investigator will also report to other institutions’ investigators.

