## **Intraoperative and Postoperative Assessment Items**

**8-2-1 Surgical Assessment Items**

1. Surgical procedure, reconstruction method
2. Operative time
3. Blood loss (from incision to closure), transfusion volume (intraoperative and until first discharge)
4. Primary tumor site
5. Tumor size
6. Depth of invasion (post-resection), lymph node metastasis (post-resection), surgical stage (post-resection)
7. Omentectomy
8. Intraoperative complications (CTCAE v3.0 Short Name and JCOG intraoperative/postoperative complication criteria): from incision to closure. The attending physician's judgment regarding causality with the treatment will also be reported.

􀂂 Intraoperative/postoperative complication criteria: pulmonary embolism, lung infarction

􀂂 Surgical/intraoperative injury: pancreas, spleen, gallbladder-common bile duct, portal vein, major arteries of organs, major veins of organs, esophagus, duodenum, jejunum, ileum, colon

􀂂 Other fatal complications

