**8-2-2 Postoperative In-Hospital Assessment Items**

1) Early postoperative complications (CTCAE v3.0 Short Name, JCOG intraoperative/postoperative complication criteria, Clavien-Dindo classification) up to 90 days postoperatively.

􀂂 Assessment items: pancreatic fistula, postoperative bleeding, intra-abdominal abscess, gastrointestinal anastomotic leakage, gastrointestinal stricture, cholecystitis, dumping syndrome, delayed gastric emptying, reflux esophagitis, obstructive ileus, paralytic ileus, thrombosis/embolism, postoperative pneumonia, pleural effusion, chylous ascites, surgical site infection, wound dehiscence, other Grade ≥3 non-hematological toxicities

2) Date of first discharge after surgery

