**8-2-3 Postoperative Assessment Items**

1) Pathological findings

􀂂 Histological type of primary lesion

􀂂 Depth of invasion, lymph node metastasis

􀂂 Proximal and distal margins

􀂂 Histopathological stage, overall curability

􀂂 Details of each lymph node metastasis

2) Recurrence status

􀂂 Regular follow-up as described below will be conducted to assess recurrence by the attending physician or study office. Recurrence sites will also be recorded.

- 1. Tumor markers (CEA, CA19-9): every 3 months for 3 years postoperatively
  2. CT of upper abdomen and pelvis: every 6 months for 3 years postoperatively
  3. Upper gastrointestinal endoscopy: once a year only for distal gastrectomy

Schedule Table

| Item | Pre-op | Post-op Observation Period | | | | | | | | | | | |
| --- | --- | --- | --- | --- | --- | --- | --- | --- | --- | --- | --- | --- | --- |
| Time | 2–4 weeks before | 3M | 6M | 9M | 1Y | 1Y  3M | 1Y  6M | 1Y  9M | 2Y | 2Y  3M | 2Y  6M | 2Y  9M | 3Y |
| Consent acquisition | ● |  |  |  |  |  |  |  |  |  |  |  |  |
| Patient background | ● |  |  |  |  |  |  |  |  |  |  |  |  |
| Subjective/objective symptoms | ● | ● | ● | ● | ● | ● | ● | ● | ● | ● | ● | ● | ● |
| Adverse events observation ^a^ |  | ● | ● | ● | ● | ● | ● | ● | ● | ● | ● | ● | ● |
| Upper GI endoscopy | ● |  |  |  | ● |  |  |  | ● |  |  |  | ● |
| CT scan | ● |  | ● |  | ● |  | ● |  | ● |  | ● |  | ● |
| Hematology tests ^b^ | ● | ● | ● | ● | ● | ● | ● | ● | ● | ● | ● | ● | ● |
| Biochemistry tests ^c^ | ● | ● | ● | ● | ● | ● | ● | ● | ● | ● | ● | ● | ● |
| Physiological function tests | ● |  |  |  |  |  |  |  |  |  |  |  |  |

M: Month、Y: Year

a: Adverse events include all undesirable events, regardless of causality with the drug.

b: Hematology tests include WBC, hemoglobin, platelet count; used to confirm safety.

c: Biochemistry tests include TP, albumin, AST, ALT, total bilirubin, creatinine, CRP, CEA, CA19-9; used to confirm safety and treatment effect.

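### Prompt SAE reporting is tied to the hospital stay, although early complications count to day 90: a death at home in that window need not be promptly reported, and readmissions depend on how the rule is read

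*Protocol*

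**What the plan says.** Section 9.2 lists death, life-threatening events and any event that "Requires or prolongs hospitalization" among its criteria for seriousness. It then has the investigator "promptly report all serious adverse events during surgery or postoperative hospitalization to the hospital director", whether or not the event is thought to be related to the study. The same paragraph adds that, in a multicenter trial, "if causality cannot be ruled out, the investigator will also report to other" institutions' investigators. It names no other reporting period.

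Section 8-2-2 asks for "Early postoperative complications (CTCAE v3.0 Short Name, JCOG intraoperative/postoperative complication criteria, Clavien-Dindo classification) up to 90 days postoperatively". Its next item is "Date of first discharge after surgery". Section 8-2-1 likewise separates the first stay from what follows when it asks for "transfusion volume (intraoperative and until first discharge)". The schedule table in 8-2-3 has adverse event observation every three months to three years, with the footnote "Adverse events include all undesirable events, regardless of causality with the drug".

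On grading, 8-2-1 lists "Intraoperative complications (CTCAE v3.0 Short Name and JCOG intraoperative/postoperative complication criteria): from incision to closure", and 8-2-2 also cites v3.0. Section 13.3 evaluates adverse events with CTCAE v4.02 and Clavien-Dindo, and asks for the grade of the events specified in Section 8.2.

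**The concern.** The protocol treats the first 90 days as the period in which a complication counts as an early one after surgery. Prompt SAE reporting is instead tied to being in hospital. Abscess, anastomotic leakage, ileus and thromboembolism are all on the 8-2-2 list, and any of them can appear or worsen after a patient goes home.

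Prompt notice is at stake. The trial is multicenter with a single treated arm. A serious event after discharge that might be linked to the lavage could reach the hospital director and the other sites only through slower routes. The report to other institutions has no window of its own, so it is unclear whether it is owed for such an event.

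**Working it through.** The plan states no figure to reproduce, so the check sets the passages side by side.

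**Inputs**
- Prompt-reporting window (9.2): surgery and postoperative hospitalization.
- Early-complication window (8-2-2): surgery to day 90, although that section is headed as in-hospital items.
- First discharge (8-2-2): a separate data item, so the hospital stay is not defined as 90 days.
- No section shown extends the reporting duty in 9.2.

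**Step 1: apply the rule to events before day 90.** The narrow reading takes 9.2 to mean the stay for the gastrectomy. The broad reading adds later admissions.

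| Event | Serious under 9.2? | Prompt report, narrow reading | Prompt report, broad reading |
| --- | --- | --- | --- |
| Serious complication before first discharge | Yes | Owed | Owed |
| Readmission for a complication | Yes | Not owed | Owed |
| Life-threatening event after discharge, not admitted | Yes | Not owed | Not owed |
| Death after discharge, not readmitted | Yes | Not owed | Not owed |

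The last two rows fall outside on either reading. The second row depends on the reading.

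**Step 2: see what else would bring prompt notice.**
- Section 9.1 requires immediate care and recording in the medical record and CRF. It sets no notification.
- The first scheduled postoperative observation in 8-2-3 is at 3 months, about when the 90-day window closes.
- Section 15.5 provides review by the study office and the Safety and Efficacy Evaluation Committee twice a year. If those looks are evenly spaced (an assumption), they are about 12/2 = 6 months apart.
- Section 10.2 lets the trial be reconsidered or stopped on safety information, but the information must first arrive.

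These secure data capture and periodic oversight. None is prompt notice.

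**Step 3: size.** The protocol gives no rate of serious events after discharge, so the number affected cannot be derived. For workload only, let p be an assumed share of the 65 planned patients with such an event before day 90. The expected number is 65 × p:
- p = 2%: 65 × 0.02 = 1.3
- p = 5%: 65 × 0.05 = 3.25
- p = 10%: 65 × 0.10 = 6.5

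These figures restate the assumption. They equal the gap only on the narrow reading; on the broad reading the gap is smaller, because readmissions drop out.

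**Step 4: CTCAE version.** Section 8-2 cites v3.0 and 13.3 cites v4.02 for the same listed events. Section 8-2 uses v3.0 as a source of short names, and 13.3 is the only section that says how to grade. The natural reading is v3.0 for names and v4.02 for grades, but the text does not say so, and 8-2-2 also asks for other toxicities of Grade 3 or higher under its v3.0 item.

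**The case against.** The strongest reply is that expedited reporting and routine data collection may properly have different windows. The intervention is a single saline lavage. Section 2.2 reports no adverse events with intraperitoneal use, and Sections 1 and 15.5 regard added harm as unlikely. Concentrating prompt reports on the hospital period is then a defensible choice. This stands in part: the differing windows are not in themselves a contradiction. It does not explain why a death on day 40 at home should be notified less promptly than one on the ward, when both lie in the protocol's own early-complication period and 9.2 asks for reports irrespective of cause.

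Four stronger readings are tempting, and the protocol does not support them.
- *All readmissions are outside the rule.* Sections 8-2-1 and 8-2-2 say first discharge when they mean the first stay. Section 9.2 has no such word, so it can cover readmissions. The fault there is ambiguity.
- *Events after discharge go unrecorded or unreviewed.* Sections 9.1, 8-2-3 and 15.5 provide recording, visits and review.
- *A definite number of patients is affected.* Any count rests on an assumed rate and on the narrow reading.
- *The two CTCAE versions distort the adverse event results.* No event is shown to change grade, and Clavien-Dindo appears in both 8-2-2 and 13.3.

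**Conclusion.** The point holds as a gap in prompt notice. On any reading of 9.2, a death or life-threatening event after discharge without readmission is outside the duty, even before day 90. Readmissions are inside only on the broad reading, which sites may or may not adopt. The report to other institutions shares the uncertainty.

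The size of the gap cannot be derived from the protocol. Data capture, the primary analysis and the sample size are unaffected. The conclusion rests on the wording of 9.2 and on no other section shown extending it. It is worth correcting because it concerns safety oversight and is cheap to close. The CTCAE mismatch is a minor clarification and does not carry the point.

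**What to change.** In Section 9.2, require prompt reporting of all SAEs from surgery to postoperative day 90. Name readmissions and deaths after discharge expressly. Exempt events due solely to recurrence or to adjuvant chemotherapy, and state that the report to other institutions follows the same window.

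The chemotherapy exemption is needed because Section 1 describes postoperative chemotherapy as standard for stage II–IIIB disease and Section 6.7 prohibits no concomitant therapy. Without it, if chemotherapy starts before day 90 (the protocol gives no timing), admissions for its toxicity would also have to be reported. The price is an attribution judgment by the investigator, and the wording should say that doubtful cases are reported.

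As a minor edit, state in 8-2 that CTCAE v3.0 supplies event names only and that grades follow v4.02 as in 13.3. Alternatively, name v4.02 throughout.

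The cost is a short amendment with ethics committee approval and a small number of extra reports through the existing route. At the assumed 2% to 10%, that concerns about 1 to 7 patients over the whole trial, on the narrow reading and before the exemptions. Any event already graded under v3.0 would need re-grading from source records.

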## **Accrual Plan**

In 2011, 20 patients met eligibility criteria at Osaka City University Hospital. Assuming a 75% consent rate, 15 patients per year are expected. Single-center accrual is insufficient for timely completion; therefore, this study will be conducted as a multicenter trial. With participation from institutions expected to enroll 5–15 patients per year, total annual accrual is estimated at approximately 35 patients. The enrollment period will be 2 years. A 3-year follow-up period after enrollment completion is required, making the total study duration 5 years.

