## **Discontinuation or Interruption of the Study**

　The principal investigator will review continuation of the study if:

1) Significant information on study drug quality, safety, or efficacy is obtained.

2) Recruitment difficulties make it impossible to achieve the target number of subjects.

3) The study objective is achieved before reaching the planned sample size or period (e.g., via interim analysis).

4) If the Data and Safety Monitoring Committee (DSMC) issues instructions to modify the protocol or other aspects of the trial, and it is judged difficult to comply with such instructions, the trial may be discontinued.

In addition, if the DSMC recommends or instructs termination, the trial will be stopped. For multicenter trials, the principal investigator or the committee specified in the protocol shall review the above matters and determine whether the trial should continue.
 When a decision is made to discontinue or interrupt the trial, the hospital director must be promptly notified in writing with the reasons.

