## **Consideration for Safety and Disadvantages**

Although the likelihood of increased adverse events due to the study treatment is considered low, these data will be collected as secondary endpoints. Monitoring will be conducted twice a year by the study office and the Safety and Efficacy Evaluation Committee to assess whether adverse events fall within the expected range.

If any adverse events occur during participation, the attending physician shall promptly take necessary measures (tests, treatment, trial discontinuation, etc.) to ensure patient safety.

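### Section 9.2 gives neither the study office nor the safety committee a prompt report of serious adverse events, although section 15.5 makes them the judges of safety and states only a twice-yearly review

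*Protocol*

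**What the plan says.** Three parts of the protocol bear on this point.

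- **Section 9.2, Reporting of Serious Adverse Events.** The events to be reported promptly are "all serious adverse events during surgery or postoperative hospitalization". They go "to the hospital director (or Clinical Trial Review Board at Osaka City University) regardless of causality with the study". Sites other than the reporting one are told under a condition: "In multicenter trials, if causality cannot be ruled out, the investigator will also report to other institutions’ investigators". The section names no other recipient.
- **Section 15.5, Consideration for Safety and Disadvantages.** "Monitoring will be conducted twice a year by the study office and the Safety and Efficacy Evaluation Committee", and the stated purpose is "to assess whether adverse events fall within the expected range".
- **Section 10.2, Discontinuation or Interruption of the Study.** The committee's decision is binding: "if the DSMC recommends or instructs termination, the trial will be stopped". This section calls the body a Data and Safety Monitoring Committee (DSMC); section 15.5 calls it the Safety and Efficacy Evaluation Committee. The text available does not say whether they are the same body.

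On pace, the Accrual Plan (section 6.3) states that "total annual accrual is estimated at approximately 35 patients", with individual institutions expected to contribute 5 to 15 a year. Section 6.2 plans 65 patients.

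**The concern.** The bodies asked to judge whether harm exceeds expectation, and the body able to stop the trial, are not among those told promptly of a serious event. The only route from one site to the others passes through a single-case causality judgement by the reporting investigator.

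That filter matters in this design. The events listed for assessment in 8-2-2, such as abscess, anastomotic leakage, bleeding and ileus, can follow any gastrectomy, so a single case can readily be put down to the operation. The study has one arm, and the Background already expects severe events from lavage to be unlikely. An excess would show mainly in the pooled rate. A site treating 5 to 15 patients a year sees only 2.5 to 7.5 in half a year and has little chance of recognising a raised rate alone. Meanwhile, patients continue to be treated at all sites.

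**Working it through.** The protocol gives no figure for the delay, so there is nothing to reproduce. The check is a comparison of routes, followed by simple arithmetic.

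**1. Who learns promptly of an in-hospital SAE, as written**

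| Body | Role | Prompt SAE report under 9.2 |
| --- | --- | --- |
| Hospital director, or Osaka City University review board | institutional oversight | yes, regardless of causality |
| Investigators at other sites | treat further patients | only if causality cannot be ruled out |
| Study office | monitors adverse events (15.5) | not named |
| Safety and Efficacy Evaluation Committee | monitors adverse events (15.5) | not named |
| DSMC | can end the trial (10.2) | not named |

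**2. Other routes in the protocol**

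- Section 5.1 requires discontinuations to be reported promptly, and section 8 counts death during protocol treatment as a discontinuation. No recipient is named. Protocol treatment is one intraoperative lavage, so a later leak or death is not clearly covered.
- Section 10.2 has the principal investigator review continuation when significant safety information is obtained. It does not say how an event judged unrelated at another site would reach that person.
- Section 13.3 has adverse events recorded on case report forms. No expedited submission is stated.

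**3. Length of the gap**

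Two reviews a year, evenly spaced: 12 / 2 = 6 months at most. For an event at a random time between two reviews, the average wait is 6 / 2 = 3 months. The protocol does not fix the spacing, so the maximum could be longer.

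**4. Patients treated during the gap, while enrolment is open**

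| Accrual basis | Per year | Maximum, 6 months | Share of 65 | Average, 3 months |
| --- | --- | --- | --- | --- |
| Section 6.3 estimate | 35 | 35 / 2 = 17.5 | 17.5 / 65 = 26.9% | 17.5 / 2 = 8.75 |
| 65 patients over the 2-year enrolment | 65 / 2 = 32.5 | 32.5 / 2 = 16.25 | 16.25 / 65 = 25.0% | 16.25 / 2 = 8.1 |

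**5. Reporting window**

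Prompt reporting in 9.2 ends with the postoperative hospital stay. Section 8-2-2 assesses early complications to 90 days, and the schedule table marks adverse event observation every 3 months to 3 years. A serious event after discharge has no prompt route in the text available.

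**The case against.** The strongest case on the other side has five parts.

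- **Events do not stay inside the hospital.** A reader might infer from 9.2 that an event judged unrelated is known only at the site where it happened. The text does not support that. It offers the Osaka City University review board as an alternative recipient regardless of causality, and for other sites such a report does leave the hospital. This stands. But the wording is an alternative rather than an additional report, and that board is not the committee of 15.5.
- **The committee's own section was not available.** The table of contents lists 19.3 for the Safety and Efficacy Evaluation Committee, but its text was not in the material reviewed. A reporting route may be set out there. This also stands, so the finding is limited to the text available. Section 9.2 should still state the route or refer to it.
- **Twice a year is a monitoring frequency.** Section 15.5 does not say that the committee sees safety data at no other time, and section 10.2 sets no calendar limit on reviewing continuation. This is fair: the half-yearly delay is what may happen under the written rule, not what must happen.
- **The risk is thought to be low.** The treatment is normal saline, and section 2.2 says that no adverse events have been reported with intraperitoneal use. That bears on how likely a problem is. It does not explain why those who judge safety are left off the prompt report.
- **Causality judgement is not shown to be poor.** A reader might infer that single-case attribution is especially unreliable for surgical complications. Nothing in the protocol establishes this, and the point does not need it. It is enough that the filter works case by case, while an excess over ordinary complications shows in pooled data.

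**Conclusion.** The point holds as a weakness in a stated rule. In the text available, section 9.2 gives no prompt SAE report to the study office or the safety committee, and the only stated contact of those bodies with adverse events is the twice-yearly monitoring in 15.5. An event that one site judges unrelated may reach them only at the next review.

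The delay is at most about six months, with up to about 16 to 18 patients (25 to 27% of 65) treated meanwhile; the average is about three months and 8 to 9 patients. These figures assume evenly spaced reviews, open enrolment, accrual of 32.5 to 35 a year, and no route in section 19.3. The larger numbers are maxima and should not be read as the expected delay.

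Two related defects belong with it: the prompt reporting window is shorter than the 90-day complication assessment, and the committee carries two names. No efficacy analysis or sample size is affected.

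**What to change.** In section 9.2:

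- Require each SAE report to be copied to the study office at the same time as it goes to the hospital director or review board, regardless of causality.
- Require the study office to forward it to the Safety and Efficacy Evaluation Committee without waiting for the half-yearly review. If section 19.3 already provides this, a cross-reference is enough.
- Reconcile the in-hospital reporting window with the 90-day assessment in 8-2-2. Otherwise the copied report inherits the same limit, and serious events after discharge still have no prompt route.

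Use one name for the committee in sections 10.2, 15.5 and 19.3, or state that there are two bodies and what each receives. Keep the twice-yearly review for cumulative data.

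The cost is a short amendment, one more addressee on a report that is already required, and a small added load for the study office and committee. If the reporting window is lengthened, sites would also file some reports after discharge.
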